#### Electric Moxibustion Treatment

Using electric moxibustion (Onttum, TechnoScience Co, Ltd), heating stimulation will be applied to the bilateral Tianshu (ST25), Zhongwan (CV12), Qihai (CV6), Guanyuan (CV4) at 40 °C mode for the duration of the acupuncture treatment (15 minutes).

#### Intradermal Acupuncture Treatment

After acupuncture and moxibustion treatments are completed, intradermal acupuncture (Press Needle, Dongbang Medical Co, Ltd) will be attached to the bilateral Yanglingquan (GB34), Zusanli (ST36), and auricular Shenmen. Patients will be instructed to frequently apply acupressure to the attachment area.

### Outcome Measurements

#### Evaluation Overview

The efficacy of acupuncture and moxibustion in managing the motor and nonmotor symptoms of PD will be evaluated using the Movement Disorder Society–Sponsored Revision of the Unified Parkinson's Disease Rating Scale (MDS-UPDRS), Berg Balance Scale (BBS), Timed Up and Go Test (TUG), Schwab and England Activities of Daily Living Scale (S&E), 39-Item Parkinson's Disease Questionnaire (PDQ-39), and levodopa dosage investigation. To assess the association between acupuncture treatment-induced changes in symptoms and gut microbiome changes in PD, we will investigate changes in gut microbiome–related metabolites through blood sampling and changes in gut microbiome through fecal sampling. Participants’ digestive symptoms will be assessed by abdominal examination, Gastrointestinal Symptom Rating Scale (GSRS), Total Dyspepsia Symptom Scale (TDS), and Bristol Stool Scale (BSS). Subjective perception of health will be assessed using the Measure Yourself Medical Outcome Profile (MYMOP). Credibility assessment in trials of acupuncture will be conducted to evaluate the impact of psychological factors on patients with PD.

#### Evaluation of Motor and Nonmotor Symptoms of PD

The MDS-UPDRS, the primary outcome of this study, was developed to complement the UPDRS as a tool to assess motor and nonmotor symptoms in patients with PD [22], and the Korean version has been validated [23]. The MDS-UPDRS comprises the following four parts with a total of 65 items: (1) nonmotor experiences of daily living, (2) motor experiences of daily living, (3) motor examination, and (4) motor complications. Of these, 48 items are scored from 0 to 4, with 0 (robust), 1 (slight), 2 (mild), 3 (moderate), and 4 (severe), and the 17 remaining items are scored as yes or no. Scores are calculated by summing the scores for each item, with higher scores indicating more severe symptoms of PD. The BBS is used to assess balance [24] and is also useful in evaluating equilibrium in patients with PD [25], and the Korean version of this tool has been validated [26]. This tool comprises 14 items that are scored from 0 (worst) to 4 (best), and the total score is evaluated. The TUG is used for assessing gait in older adults [27] and is used to evaluate walking ability in patients with PD [28]. This test measures the time taken to get up from a chair, walk around a 3-meter return point, and return to the chair in the initial position. The S&E is a component of the UPDRS that evaluates functional independence and is widely used as a standard Parkinson assessment tool [29]. The patient’s function is evaluated using an 11-point scale with 10% increments, from 100% (completely independent) to 0% (vegetative functions are not functioning or bedridden). The PDQ-39 is used for assessing health-related quality of life (HrQoL) in patients with PD [30], and the Korean version has been validated [31]. The PDQ-39 comprises 8 dimensions with 39 items. Each item is scored from 0 (never) to 4 (always), with a higher total score indicating poorer HrQoL due to PD. Levodopa dosage investigation includes assessment of the daily dose and number of levodopa doses administered to patients with PD. Changes in type and dose of levodopa from pretreatment will be investigated first as “yes or no” and then dichotomized into “decrease or increase” for participants with no change for comparison between groups. Evaluation will be conducted at day 0, 6 weeks, 12 weeks, and 20 weeks in participants with PD and after screening in healthy participants.

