### Recruitment

For the study, 20 healthy participants and 60 patients with PD will be recruited through walk-ins or hospital and school bulletin boards, public transportation billboards, newsletters, and other online advertisements. Participants who wish to participate will receive an explanation of the consent form, provide written consent of their own free will, and participate in the study if the researcher determines that they are suitable through a screening process. The screening items are as follows: demographic information, medical history, PD diagnosis, treatment history, medications, vital signs, Hoehn and Yahr stage assessment, and inclusion and exclusion criteria evaluation (Table S1 in Multimedia Appendix 1 and Table 1 on code rather than the participant's name.

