### Statistical Analysis

#### Overview of Statistical Analysis

SPSS (ver 21.0, IBM SPSS Statistics for Windows) will be used for analysis. All measures will be presented as mean (SD) for continuous variables and as n (%) for dichotomous variables. For efficacy endpoints, the amount of change or rate of change from baseline to end of treatment and follow-up will be calculated.

All data obtained from participants will be analyzed in 2 forms: intention-to-treat (ITT) analysis and per-protocol (PP) analysis. The ITT analysis will be performed on all participants who undergo acupuncture and moxibustion at least once. For missing data on the evaluation variables, the last observation carried forward (LOCF) method will be applied. PP analysis will further be performed on participants who completed the entire study. The evaluation will be based on the results of the ITT analysis and is presented with reference to the PP analysis.

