#### Analysis for Changes in Clinical Outcomes

For the following clinical outcomes with continuous variables, the mean (SD), median, minimum, maximum, and maximum of each outcome will be presented for change in score from day 0 to 6 weeks, 12 weeks, and 20 weeks, and a 1-way repeated measures ANOVA will be performed to test for statistically significant changes in any of the following factors: total MDS-UPDRS score, total MDS-UPDRS score part I score, total MDS-UPDRS part II score, total MDS-UPDRS part III score, total MDS-UPDRS part IV score, BBS, TUG, S&E, PDQ-39, levodopa dosage investigation, abdominal examination, GSRS, TDS, BSS, and MYMOP.

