This study has limitations that must be weighed when interpreting the findings. Nutritional management is recommended for patients with PD, including dietary distribution to optimize levodopa absorption, dietary interventions for the improvement of nonmotor symptoms, and regular monitoring of food intake [57]. This leads to differences in dietary habits between PD patients and robust people, with PD patients showing higher protein and higher fiber dietary habits than robust people [58]. Fibers activate various beneficial microbiomes and suppress harmful species, and protein also has a significant impact on the gut microbiome [59]. Since this study does not investigate the nutritional intake of PD patients and healthy individuals, the influence of dietary differences should be considered when comparing the gut microbiome results between the two groups. Furthermore, levodopa dosage may affect gut microbiome composition [60]. Although this study investigates levodopa dosage in PD patients as part of clinical outcomes, it does not exclude the potential confounding effect of dosage adjustment on the gut microbiome. Therefore, any significant changes in levodopa dosage should be taken into consideration in the results.

The study will generate data on the effects of acupuncture and moxibustion on gut microbiome of patients with PD and explore its association with improvement in clinical symptoms. If the study results demonstrate that acupuncture and moxibustion change the gut microbiome in patients with PD, it will be the first clinical evidence to support a microbiome-gut-brain axis mechanism for acupuncture and moxibustion treatment of PD, ultimately contributing to the potential of acupuncture and moxibustion as an alternative treatment for PD.

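### The drug-change outcome follows levodopa only, although patients qualify on any non-anticholinergic anti-Parkinson agent, so changes in other agents are scored as no change or as a levodopa decrease

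*Protocol article*

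**What the plan says.** **Who enters.** The inclusion criteria for patients with PD (Eligibility) ask for more than 5 years on anti-Parkinson agents, anticholinergics excepted. No criterion requires levodopa.

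**What is measured.** Under Evaluation of Motor and Nonmotor Symptoms of PD: "Levodopa dosage investigation includes assessment of the daily dose and number of levodopa doses administered to patients with PD". Change from pretreatment in the type and dose of levodopa is coded first as yes or no, then by direction. Assessment is at day 0 and weeks 6, 12 and 20.

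**How it is used.** The same section names "The MDS-UPDRS, the primary outcome of this study". Evaluation Overview introduces its instruments with "The efficacy of acupuncture and moxibustion in managing the motor and nonmotor symptoms of PD will be evaluated using", and the levodopa dosage investigation is on that list. In Analysis for Changes in Clinical Outcomes, "a 1-way repeated measures ANOVA will be performed to test for statistically significant changes in any of the following factors"; levodopa is the only drug item among those factors, and no medication covariate is stated.

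**Where other drugs appear.** Recruitment lists the screening items: "demographic information, medical history, PD diagnosis, treatment history, medications, vital signs, Hoehn and Yahr stage assessment". The dropout criteria cover other drugs that could affect results, if taken without the study physician's agreement. The Discussion treats levodopa dose as a possible confounder of the microbiome and concludes: "Therefore, any significant changes in levodopa dosage should be taken into consideration in the results". It does not mention other anti-Parkinson agents.

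**The concern.** The population is defined on a drug class and the on-study drug measure on one member of it. The Eligibility section itself gives response to anti-Parkinson agents as the reason why an added effect of acupuncture is hard to isolate, so the class as a whole is what needs following.

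Two results are exposed. There is no PD control arm and no blinding, so a change in a non-levodopa agent between day 0 and week 20 becomes part of the within-group MDS-UPDRS change. It also enters the correlations between symptom change and microbiome change. In addition, the levodopa outcome is itself listed under efficacy, so a patient moved from levodopa to another agent contributes a decrease that a reader could take as favourable.

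**Working it through.** The plan gives no figure to reproduce: the sample size is set by feasibility, with no effect size, SD or power. The check is a comparison of the text, followed by an illustration of scale.

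**Step 1: what the outcome records, taken as written.** The direction step is worded as applying to participants with no change; I read it as meant for those who changed.

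| Event after day 0 | Recorded by the levodopa outcome |
|---|---|
| Levodopa constant, another agent raised or lowered | No change |
| Levodopa lowered, another agent raised | Levodopa decrease |
| Patient not on levodopa, another agent changed | Dose 0 throughout, no change |

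The third patient does have a value, namely zero, but it carries no information about drug change.

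**Step 2: do other provisions close the gap?**
- The dropout rule reaches only drugs taken without the study physician's agreement. Agreed changes stay in.
- For patients who do leave, "the last observation carried forward (LOCF) method will be applied" in the intention-to-treat analysis, so their earlier values are kept.
- Medications are listed at screening. Whether they are recorded again at later PD visits depends on Table S1, which is not shown.
- The limitation on dose changes concerns levodopa and the microbiome, not other agents and not MDS-UPDRS.

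**Step 3: scale.** All rates, effects and SDs here are assumptions; only n = 60 comes from the protocol. Let f be the share of patients with a change in another agent and d the resulting change in MDS-UPDRS points. If all changes run one way, bias in the mean = f × d.

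- Low: 60 × 0.05 = 3 patients; 0.05 × 3 = 0.15 points.
- High: 60 × 0.20 = 12 patients; 0.20 × 8 = 1.6 points.

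If changes run both ways, the net bias is f(up) × d(up) − f(down) × d(down). With 10% each way at 5 points, 0.10 × 5 − 0.10 × 5 = 0.

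**Step 4: effect on a test of one change from baseline.** This uses a paired normal approximation, two-sided 0.05, with no true acupuncture effect. It stands in for the four-time-point ANOVA.

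SE = √{[SD² + f(1 − f)d²] / 60}; rejection probability = Φ(bias/SE − 1.96) + Φ(−bias/SE − 1.96).

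| f | d | SD of change | Bias | Chance of a significant change |
|---|---|---|---|---|
| 5% | 5 | 15 | 0.25 | 5.2% |
| 10% | 10 | 15 | 1.0 | 8.0% |
| 20% | 10 | 15 | 2.0 | 17% |
| 30% | 10 | 10 | 3.0 | 56% |

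For the third row: SE = √[(225 + 0.16 × 100)/60] = √(241/60) = 2.00, so bias/SE is about 1.0 and the result is about 17%. These are one-directional changes; the last row is an extreme case.

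**The case against.** A reader might infer that non-levodopa changes go unrecorded and that their effect will be reported as an effect of acupuncture. The documents do not support either statement.

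- **Recording.** The PD visit schedule is in an appendix that is not shown. The healthy participants' schedule (Table 1) has a separate medications row, and the PD schedule may repeat one at later visits. Applying the dropout rule also implies some watch on other drugs. All that can be said is that the defined and analysed outcome omits them.
- **Interpretation.** Sample Size says that the study does not set out to prove an intervention effect, and the Discussion concedes weak internal validity and compromised causal inference. This softens the concern, although Evaluation Overview still calls these measures efficacy. No passage says that a levodopa decrease will be counted as benefit.
- **Size and direction.** The magnitudes are assumed. MDS-UPDRS has 48 items scored 0 to 4, a maximum of 48 × 4 = 192, so 0.15 to 1.6 points is about 0.08% to 0.8% of the range. Reductions in other agents would hide improvement rather than create it.
- **Feasibility.** Observation had ended by February 19, 2025, so nothing further can be collected at the study visits.

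These points limit the claim and the remedy. They leave the mismatch standing: this is a measure positively defined on too narrow a base, not detail that an article has left to a longer document.

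**Conclusion.** The concern holds in limited form. Followed as written, the drug-change outcome scores a change in another anti-Parkinson agent as no change and a switch away from levodopa as a decrease. With no PD comparator and no stated medication adjustment, such changes could bias the MDS-UPDRS and symptom-microbiome results in either direction.

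The size cannot be determined from the documents. On the assumptions shown, it is negligible if few patients changed other agents and material if a fifth or more changed in the same direction. The conclusion does not rest on those figures, and it does not establish that other agents went unrecorded or that any particular result is wrong. It warrants a correction before results are reported; it does not invalidate the study.

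**What to change.** 1. From the medication data already recorded, derive total levodopa-equivalent daily dose across all anti-Parkinson agents at day 0 and weeks 6, 12 and 20, with levodopa dose as a component. State the conversion factors used.
2. Classify each patient as decreased, unchanged or increased on that total.
3. Repeat the MDS-UPDRS and symptom-microbiome analyses in patients with no change in any anti-Parkinson agent. Label this as a sensitivity analysis added after data collection.
4. If non-levodopa doses were not recorded after screening, extend the Discussion's limitation to all anti-Parkinson agents and to the symptom outcomes, and do not interpret a levodopa decrease alone as benefit.

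The cost is some extra data work and a smaller subset for the sensitivity analysis, with correspondingly less precision. Patient care is unaffected. If the later doses do not exist, only step 4 is available.

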## Methods

### Study Design

This protocol describes a single-group, prospective, observational study aiming to analyze differences in gut microbiome between patients with idiopathic PD and healthy participants, to observe changes in gut microbiome after 12 weeks of acupuncture and moxibustion in patients with PD, and to correlate these changes with changes in motor and nonmotor symptoms of PD that were altered by acupuncture and moxibustion treatment. The gut microbiome patterns at baseline in healthy participants and screened patients with PD will be analyzed to determine whether the gut microbiome of patients with PD is different from that of healthy participants. Patients with PD will be treated with acupuncture, moxibustion, and intradermal acupuncture twice a week for 12 weeks, yielding a total of 24 sessions. The motor and nonmotor symptoms of PD and gut microbiome changes in response to acupuncture and moxibustion will be compared before starting treatment (day 0), during treatment (6 weeks), at the end of treatment (12 weeks), and 2 months after the end of treatment (20 weeks). The correlation between motor and nonmotor symptoms of PD changed by acupuncture and moxibustion treatment and changes in gut microbiome will be analyzed. The enrollment, interventions, and assessments of patients with PD are summarized in Table S1 in Multimedia Appendix 1. A schematic of the study process is shown in Figure 1. Healthy participants will be assessed for motor and nonmotor symptoms of PD and gut microbiome after screening. The enrollment and assessment of healthy participants are summarized in Table 1. Kyung Hee University Korean Medicine Hospital, Seoul, Republic of Korea, will serve as the study site. The study protocol was registered with the Clinical Research Information Service (KCT0006669) on October 15, 2021. This protocol was reported in accordance with the SPIRIT (Standard Protocol Items: Recommendations for Interventional Trials) guidelines (Multimedia Appendix 2).

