#### Evaluation of Digestive Symptoms

Abdominal examination is a Korean medicine diagnostic method based on the Korean medicine theory that when a disease is inside the body, its response manifests on the body surface [32]. Participants will undergo manual palpation of Zhongwan (CV12) and Tianshu (ST25) for tenderness, while the presence or absence of gastric stuffiness and rigidity below the heart will be checked. The GSRS is a globally used self-reported gastrointestinal symptom scale that covers upper and lower gastrointestinal symptoms [33]. It comprises 15 questions in 5 domains (abdominal pain, reflux syndrome, indigestion syndrome, diarrhea syndrome, and constipation syndrome) scored on a 7-point scale from 1 (no symptoms) to 7 (very severe symptoms). The TDS has been used in previous studies to assess functional dyspepsia [34,35] and comprises 8 items (postprandial fullness and bloating, early satiety, epigastric pain, epigastric burning, nausea, vomiting, belching, and other symptoms) rated on a scale of 0 (absent) to 3 (severe). The BSS is the most widely used measure of stool formation, ranging from the hardest (type 1) to the softest (type 7) [36]. Evaluation will be conducted at day 0, 6 weeks, 12 weeks, and 20 weeks in participants with PD and after screening in healthy participants.

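### The levodopa change rule cannot be applied as written, and presence/absence abdominal signs and stool type are listed as continuous outcomes

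*Protocol article*

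**What the plan says.** **Levodopa.** In Evaluation of Motor and Nonmotor Symptoms of PD, what is collected is numeric: "Levodopa dosage investigation includes assessment of the daily dose and number of levodopa doses administered to patients with PD". Change in type or dose from pretreatment is then coded in two steps, first yes or no, and then as a decrease or an increase "for participants with no change for comparison between groups". Study Design states: "This protocol describes a single-group, prospective, observational study".

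**Abdominal examination and stool type.** In Evaluation of Digestive Symptoms, the examination includes palpation for tenderness at two named points, and "the presence or absence of gastric stuffiness and rigidity below the heart will be checked". The Bristol Stool Scale (BSS) is described there as types 1 to 7, hardest to softest.

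**Analysis.** Analysis for Changes in Clinical Outcomes opens its list with "For the following clinical outcomes with continuous variables". It asks for mean (SD), median, minimum and maximum of the change scores and then says "a 1-way repeated measures ANOVA will be performed to test for statistically significant changes in any of the following factors". The list includes the levodopa investigation, the abdominal examination and the BSS. Overview of Statistical Analysis says that dichotomous variables are to be reported as n (%).

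**The concern.** There are two separate faults.

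1. The second step of the levodopa coding is attached to the wrong people. The article's Discussion says that levodopa dosage may influence the gut microbiome, that the study does not exclude confounding by dose adjustment, and that significant dose changes must be considered in the results. The variable meant to support that reading should therefore be usable. The between-group comparison also has nothing to refer to.

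2. Yes/no signs and an ordered stool type are treated as continuous. For the signs, this contradicts the article's own reporting rule for dichotomous variables. For stool type, the average of signed changes need not measure improvement. Both belong to the digestive outcomes, and clinical outcomes are later to be correlated with key microbiome features.

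**Working it through.** The article gives no power, effect size or other figure on this point, so there is nothing to reproduce. The levodopa rule is checked by logic, the ANOVA by simulation, and the BSS by a constructed example.

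**1. Levodopa rule**

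- Step 1 splits PD patients into change = yes and change = no.
- Step 2 assigns decrease or increase within change = no. By definition nobody there has either.
- Patients with change = yes receive no direction.

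Illustration with assumed counts: of 60 patients, 40 are unchanged, 12 lower and 8 higher. As written, the 40 unchanged are eligible for a direction and yield 0 decreases and 0 increases. The 12 + 8 = 20 changers stay unclassified. The result is the same for any counts.

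Between groups: there is one treated group. Healthy participants have one outcome assessment, Table 1 lists no levodopa investigation for them, and a diagnosis of PD excludes them. No levodopa change from pretreatment exists outside the PD group.

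**2. Repeated-measures ANOVA on a yes/no sign**

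Inputs from the article: 60 PD patients and 4 time points (day 0, weeks 6, 12 and 20). Assumed: prevalence 0.5, 0.2 or 0.05; latent correlation compound symmetric 0.5 or AR(1) 0.7; no true change; level 0.05 (stated for the microbiome and metabolite tests, assumed here). There were 4,000 runs per setting, so the Monte Carlo standard error is about √(0.05 × 0.95 / 4000) = 0.0034.

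| Prevalence | Correlation | ANOVA | ANOVA, Greenhouse-Geisser | Cochran's Q |
|---|---|---|---|---|
| 0.5 | CS 0.5 | 0.052 | 0.049 | 0.051 |
| 0.5 | AR(1) 0.7 | 0.058 | 0.051 | 0.057 |
| 0.2 | CS 0.5 | 0.049 | 0.044 | 0.047 |
| 0.2 | AR(1) 0.7 | 0.051 | 0.043 | 0.050 |
| 0.05 | CS 0.5 | 0.038 | 0.021 | 0.035 |
| 0.05 | AR(1) 0.7 | 0.051 | 0.032 | 0.049 |

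Uncorrected ANOVA gives 0.038 to 0.058, and Cochran's Q gives 0.035 to 0.057. With the correction, the ANOVA becomes conservative for a rare sign.

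The summary is what fails. A 0/1 sign has mean p and SD √(p(1 − p)); at p = 0.2 the SD is √0.16 = 0.40, which adds nothing to the proportion. Its change score can only be −1, 0 or +1, so the mean change is the net difference and hides how many patients gained and how many lost the sign.

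**3. Mean signed BSS change**

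Assume 30 of 60 patients move to type 4, a of them from type 2 (+2 each) and b from type 6 (−2 each). Mean change = (2a − 2b)/60.

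| a (hard) | b (loose) | Mean change |
|---|---|---|
| 30 | 0 | 60/60 = 1.00 |
| 20 | 10 | (40 − 20)/60 = 0.33 |
| 15 | 15 | (30 − 30)/60 = 0 |

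The same number of patients reaches mid-scale in every row, but the mean runs from 1.00 to 0. With no loose stools there is no cancellation.

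**The case against.** The case on the other side is substantial.

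- *The levodopa sentence is a slip.* A yes/no step followed by a direction has one workable reading, namely direction for those with a change. Since daily dose is recorded at each evaluation, direction can be derived for every patient. This stands as far as the data go: nothing is lost. It does not rescue the stated rule, and the between-group phrase stays without a referent. If groups of dose changers were meant, the article defines none.
- *Levodopa belongs in the ANOVA list.* This stands. Daily dose is numeric, so listing levodopa as continuous is not an error. The text only needs to say which levodopa variable is tested, because the coding described is categorical.
- *The tests are valid.* A reader might infer that ANOVA on yes/no signs gives invalid P values, or that these results will be meaningless. The simulation does not support that at 60 patients.
- *Tenderness may be graded.* This stands. Presence/absence is stated only for stuffiness and rigidity, and the tenderness scale may be in a fuller document.
- *BSS cancellation is hypothetical.* Largely stands. The article does not call mid-scale the goal, names constipation as its example of a gastrointestinal symptom, and includes constipation but not diarrhea among its symptom-specific acupuncture points. The Gastrointestinal Symptom Rating Scale also covers the two separately. A reader might infer that cancellation will occur, but the document does not show a sizeable loose-stool subgroup.
- *None of this is primary.* This stands: MDS-UPDRS is the primary outcome, and the Sample Size section calls the study exploratory.

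**Conclusion.** The point holds in a limited form.

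- **Levodopa:** the written rule classifies no dose changer by direction and refers to a comparison that the design does not contain. This conclusion is purely logical and needs no assumption. Its weight comes from the Discussion's reliance on levodopa change when the microbiome results are read.
- **Abdominal signs:** stuffiness and rigidity are yes/no, yet are set for mean (SD) and ANOVA, against the article's own n (%) rule. The fault is an unsuitable summary and estimate. Type I error stays near 5% under the assumed prevalences and correlations.
- **BSS:** an ordered scale is treated as continuous, and its mean signed change can mask opposite movements if both hard and loose stools are present. How far this happens here is unknown.

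Severity is minor to moderate. The three variables are secondary, but the stated rule and the stated analyses do not fit them.

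**What to change.** 1. **Levodopa coding.** Classify each visit against day 0 as decreased, unchanged or increased in daily dose, giving a direction only to those with a change. Compare over time within PD patients and delete the between-group wording. A change of type alone has no direction and can be reported as yes/no.
2. **Levodopa in the ANOVA.** Name total daily dose as the variable analysed.
3. **Abdominal signs.** Take the presence/absence signs out of the continuous list. Report n (%) per sign and visit, with Cochran's Q followed by McNemar tests, or a logistic GEE with visit as factor and clustering by patient.
4. **BSS.** Use an ordinal repeated-measures model or a Friedman-type test, or predefine hard, middle and loose categories and report movement between them.

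The cost is a few sentences and a few model calls on data already collected. The Results section says analysis is in progress, so the definitions should be fixed and dated before these outcomes are examined. If they have already been examined, the change should be reported as made afterwards.
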